### Statistical analysis

186 (62 per group) participants were calculated using a 5 % significance level with a variance and change of 0·2 in the MetS-Z score after a 12-week cardioprotective diet and exercise programme by Hickman *et al*.^(47)^ based on 80 % power with G*Power software^(48)^ for our parallel RCT design. A total of 222 participants will be recruited to account for 20 % drop out. Final data will be analysed using intention-to-treat analyses with a linear mixed model (SPSS, IBM), and covariates (age, weight loss) will be added to the model if required in consultation with a biostatistician. Data will be coded and remain blinded to outcome assessors until all analyses are completed. Statistical significance will be considered as a *p* value
<
 0·05.

In addition, a per-protocol secondary analysis will be conducted. Compliance with the LC interventions (CHO 35 
±
 10 % energy) will be assessed using the two weighed food records and weekly checklists/Easy Diet Diary data. Mediterranean diet adherence will be estimated using average of the MEDAS scores across the study, weekly checklists/Easy Diet Diary data and weighed food records, that is, overall, attaining high consumption of monounsaturated fatty acids; daily consumption of fruits, vegetables, whole grains, fibre, weekly consumption of fish, poultry, nuts and legumes; a relatively low consumption of red meat; and moderate consumption of alcohol^(49)^. MEDAS scores of 8 or above in the Mediterranean arms, which is considered moderate adherence in most studies/trials^(50)^, will be included in the analysis.

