### Study integrity

This study will be conducted according to the guidelines in the Declaration of Helsinki, and all procedures involving human participants were approved by the University of Wollongong and Illawarra Shoalhaven Local Health District Human Research Ethics Committee (2021/204). Written informed consent will be obtained from eligible participants prior to data collection by the study co-ordinator. The study was developed as per the CONSORT guidelines and is registered with the Australian New Zealand Clinical Trials registry (ACTRN12622000211763p) at https://www.anzctr.org.au/.

Participants will be randomised in a 1:1:1 allocation, stratified for sex using uneven blocks, to one of the three dietary intervention arms. Allocation will be generated by the statistician, and the Excel file access will be shared with the clinical trials manager in the Clinical Trials Research Unit. The study co-ordinator will generate the alphanumeric code and receive the assigned intervention from the clinical trials manager prior to a participant’s baseline visit.

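### Recruiting 222 does not cover the stated 20% dropout: it leaves about 178 completers (59 per arm), against the 186 (62 per arm) the power claim needs.

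*Protocol article*

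**What the plan says.** The Statistical analysis section of the protocol article first gives the number needed for the primary outcome, the MetS-Z score: "186 (62 per group) participants were calculated using a 5 % significance level", "with a variance and change of 0·2 in the MetS-Z score", "based on 80 % power with G*Power software". It then moves from that requirement to the recruitment target in one step: "A total of 222 participants will be recruited to account for" 20% dropout.

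The abstract repeats the total of 222. The Study integrity section sets the allocation: "Participants will be randomised in a 1:1:1 allocation, stratified for sex using uneven blocks". That makes 74 per arm at 222. Nowhere does the article give a different dropout rate or say that 186 already contains an allowance for loss.

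**The concern.** A dropout allowance applies to the people recruited, so the number needed must be divided by the proportion expected to remain. Here 186 divided by 0.80 is well above 222. The printed total looks instead like the requirement multiplied by 1.2, a common slip that always gives too few.

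At stake is whether the three printed figures (186 needed, 20% lost, 222 recruited) can stand together. If they cannot, the trial has less protection against loss than it says, and power at the planned dropout is below the stated 80%. Readers of the results will also use this sentence to judge whether the trial met its target.

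**Working it through.** **Inputs, all from the protocol article**

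- Required with outcome data: 186, or 62 per arm (Statistical analysis).
- Dropout allowance: d = 0.20 (Statistical analysis).
- Recruitment target: 222 (Statistical analysis; Abstract).
- Allocation: 1:1:1 (Study integrity), so 222 / 3 = 74 per arm.
- Change 0.2, variance 0.2, 5% level, 80% power (Statistical analysis). Whether the test is one- or two-sided is not stated.

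**Step 1. Reproduce the printed 222**

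Multiplying by (1 + d): 62 × 1.2 = 74.4. Rounded down this is 74 per arm, and 3 × 74 = 222 exactly. Applied to the total, 186 × 1.2 = 223.2, so even this rule gives 224 if rounded up. The article does not say how 222 was obtained; this is the likely route because it lands on the figure exactly.

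**Step 2. The number that matches 20% loss**

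N = n / (1 − d).

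- Total: 186 / 0.80 = 232.5, so 233.
- Per arm: 62 / 0.80 = 77.5, so 78, and 3 × 78 = 234.

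The printed target is 11 below 233 and 12 below 234.

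**Step 3. What 222 delivers**

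- Total at 20% loss: 222 × 0.80 = 177.6, about 178. The shortfall is 186 − 178 = 8.
- Per arm at 20% loss: 74 × 0.80 = 59.2, about 59 (three arms of 59 make 177). The shortfall is 3 per arm.
- Largest loss that still leaves 186: 1 − 186 / 222 = 0.162, or 16.2%.

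**Step 4. The cost in power**

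The basis of the 62 matters for this step only. For two means, n per arm = 2σ²(z_α + z_β)² / δ². With σ² = 0.2 and δ = 0.2 the leading factor is 2 × 0.2 / 0.04 = 10.

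- One-sided 5%: 10 × (1.645 + 0.842)² = 61.8, so 62. This reproduces the plan's base figure.
- Two-sided 5%: 10 × (1.960 + 0.842)² = 78.5, so 79. This does not.

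Power at 59 per arm was therefore computed on several bases, the first three of which give about 80% at 62 per arm:

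| Basis | 62 per arm | 59 per arm |
|---|---|---|
| One-sided z, variance 0.2 | 80.1% | 78.4% |
| Two-sided t, SD set to 0.394 so that 62 gives 80% | 80.0% | 78.0% |
| Three-arm ANOVA, f = 0.229 so that 186 gives 80% | 80.0% | 77.8% (177 in total) |
| Two-sided t, variance 0.2 taken literally | 69.5% | 67.3% |

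In each row the dropout error costs about 2 points. In the last row, most of the distance from 80% comes from the base figure of 62, which is a separate matter; only 69.5 − 67.3 = 2.2 points belong to dropout.

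**The case against.** The arithmetic is not in dispute; the case on the other side is about how much it matters.

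- **The loss is small.** About 3 completers per arm and 2 points of power change neither the hypothesis, the outcome nor the analysis. This stands, and it sets the weight of the point.
- **20% is only a planning allowance.** At any loss up to 16.2%, 222 still yields 186. True, but the sentence claims cover for 20%, and that claim fails.
- **Loss need not be equal across arms.** Also true: 59 per arm assumes equal loss. The total of 177.6 does not depend on that assumption.
- **The analysis is intention-to-treat with a linear mixed model, so dropouts stay in.** A participant with only a baseline value can stay in the model. However, the primary outcome is measured only before and after the intervention, so someone without a 12-week value adds little to the comparison between arms. The plan's own inflation for dropout also treats completers as what power depends on.
- **Adjusting for baseline could recover the loss.** If 0.2 is the variance of the change score and the model conditions on baseline, the required number falls by a factor (1 + r) / 2, where r is the pre-post correlation. The shortfall ratio is 59.2 / 62 = 0.955, so any r below about 0.91 would offset it. The article states neither r nor how baseline is handled, so this shows only that the true power is uncertain. It does not make the printed figures agree.

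**Conclusion.** The point holds. With 186 required and 20% of recruits lost, 222 is too few: it leaves about 178 (59 per arm), and the matching target is 233, or 234 with equal arms. As printed, 222 covers 16.2% loss.

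The completer count rests only on the plan's own three figures, with equal loss assumed for the per-arm number. The power figure of about 78% assumes further that 62 per arm gives 80% on the sponsor's own basis. The sentence is wrong and should be corrected, but this is a minor correction: about 8 completers and about 2 points of power.

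**What to change.** Correct the sentence in the Statistical analysis section in one of these ways.

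1. Keep 222 and state that it allows for about 16% dropout (222 × 0.84 = 186.5). No extra participants and no new power calculation.
2. Keep 222 and 20%, state that about 177 completers (59 per arm) are expected, and give the power at 59 per arm. This is about 78% if 62 per arm gives 80%. State the sidedness and the variance used, because the answer depends on them. No extra participants.
3. Keep 186 completers and 20%, and raise the target to 234 (78 per arm), in the abstract as well. This means 12 more participants within a recruitment period set to end in December 2025.

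The first two cost one sentence. The third is needed only if the sponsor wants both the 186 completers and the 20% allowance.

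### The named covariates are age and weight loss; neither sex (the stratification factor) nor baseline MetS-Z is named, which may cost precision

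*Protocol article*

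**What the plan says.** Under Study integrity, allocation is 1:1:1 and "stratified for sex using uneven blocks"; no other stratification factor is given.

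Under Study design and overview and again under Primary outcome, MetS-Z is to be assessed in everyone before and after the 12 weeks. The Primary outcome section also lists the inputs to the score, among them sex and BMI.

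Under Statistical analysis, "Final data will be analysed using intention-to-treat analyses with a linear mixed model", and "covariates (age, weight loss) will be added to the model" if this is judged necessary after consulting a biostatistician. The section does not say whether baseline MetS-Z is a response, a covariate or part of a change score. On sample size it states "186 (62 per group) participants were calculated using a 5 % significance level". The calculation takes 0.2 for both the change in MetS-Z and its variance, from an earlier diet and exercise study, and makes no stated allowance for baseline adjustment.

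**The concern.** When a plan names covariates, one expects the factor that governed the randomisation and the baseline value of the outcome to come first. Here neither appears.

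- **Sex.** Stratifying balances the arms on sex. An analysis that ignores sex takes no credit for that balance, so its standard errors are too large if sex predicts the outcome. The result is conservative rather than biased.
- **Baseline MetS-Z.** This is likely to be the best single predictor of week-12 MetS-Z. Depending on how the mixed model is built, leaving it out of the adjustment can cost power and leave the contrast exposed to chance baseline imbalance.
- **Weight loss.** This is on the list but is measured after randomisation, may be changed by the diets, and enters MetS-Z through BMI. Adjusting for it could remove part of the diet effect. That is a risk of bias and not merely of lost precision.

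Because the additions are conditional, the primary model also stays open to later choice.

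**Working it through.** **Inputs from the article:** alpha 5 % (sidedness not stated), power 80 %, change 0.2, variance 0.2, 62 per group. **Assumed, because not given:** pre-post correlation r from 0.5 to 0.9; equal variance at both visits; sex explaining 0 to 5 % of residual variance.

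**1. The plan's own figure.** For two means, n per arm = 2(z_α + z_β)² × variance / change².
- One-sided: 2 × (1.645 + 0.842)² × 0.2 / 0.04 = 61.8, so 62 per arm and 186 in total, as stated.
- Two-sided: 2 × (1.960 + 0.842)² × 0.2 / 0.04 = 78.5, so 79 per arm. Power at 62 per arm is then 70.2 %.

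Sidedness is a separate matter. Both versions are carried below.

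**2. Variance with and without baseline adjustment.** Let σ² be the variance of one score.
- Change score: 2σ²(1 − r). An unconstrained arm-by-time model on two visits gives the same contrast with complete data.
- Baseline-adjusted: σ²(1 − r²).
- Ratio: (1 − r²) / [2(1 − r)] = (1 + r)/2.

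As a check, generalised least squares at 62 per arm, with 0.2 as the variance of change, gives a contrast variance of 0.00645 for the unconstrained model. With a common baseline mean it gives 0.00484, 0.00548, 0.00581 and 0.00613 at r = 0.5, 0.7, 0.8 and 0.9. These match the formula.

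**3. What the ratio means here, if 0.2 is the variance of change:**

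| r | Variance ratio | n per arm, one-sided (from 62) | n per arm, two-sided (from 79) | Power at 62, one-sided (from 80.1 %) | Power at 62, two-sided (from 70.2 %) |
|---|---|---|---|---|---|
| 0.5 | 0.75 | 47 | 59 | 89.1 % | 82.0 % |
| 0.7 | 0.85 | 53 | 67 | 85.4 % | 77.1 % |
| 0.8 | 0.90 | 56 | 71 | 83.6 % | 74.7 % |
| 0.9 | 0.95 | 59 | 75 | 81.9 % | 72.4 % |

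The saving is 3 to 15 participants per arm one-sided, or 4 to 20 two-sided.

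**4. If 0.2 is instead the variance of a single score,** the ratio is unchanged but the power figures move. Two-sided at 62 per arm, change score against baseline-adjusted: 70.2 % against 82.0 % at r = 0.5, 89.5 % against 93.7 % at r = 0.7, and 97.6 % against 98.6 % at r = 0.8.

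**5. If the mixed model already has a common baseline mean,** it is the adjusted analysis, and naming baseline as a covariate gains nothing.

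**6. Sex.** Multiply the variance 0.2 by (1 − R²). For R² of 1, 2 and 5 %, the one-sided n per arm is 62, 61 and 59, and two-sided power at 62 is 70.6, 71.1 and 72.4 %. Sex is constant within a participant. In an unconstrained two-visit model with complete data, a sex main effect alone therefore leaves the arm-by-time contrast unchanged; a sex-by-time term is needed.

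**The case against.** The article is a condensed account, and an analysis plan that lists every fixed effect may exist. The text says only that a linear mixed model will be used, with some covariates added conditionally; it does not present those covariates as the complete model. With MetS-Z measured at both visits, such a model would normally carry baseline as a response, so baseline need not be named as a covariate. The score already uses sex, which plausibly leaves sex little residual predictive value.

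Most of this stands, and it limits the claim. A reader might infer that sex and baseline are excluded, that 10 to 25 % of the variance is therefore wasted, and that up to a third more participants' worth of information (1/0.75 = 1.33) is there for the taking. The documents do not support that. Not naming a term is not excluding it; the unconstrained model appears nowhere in the text; the loss is zero under a common baseline mean and only 5 % at r = 0.9; and the 33 % figure needs both r = 0.5 and the unconstrained form.

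What the objection does not remove is that the article goes beyond silence. It names candidate covariates, passes over the one factor that controlled allocation, includes a post-randomisation variable, and makes the additions depend on later judgement. An analysis plan that did this well would have to depart from that sentence.

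**Conclusion.** The point holds in conditional form. The named covariates are a poor choice for this design: they omit sex and baseline MetS-Z and include weight loss.

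- **Baseline:** adjustment gains between nothing (common baseline mean already used) and 5 to 25 % of the variance (unconstrained model, r from 0.9 to 0.5). The correlation is assumed and the model form is not stated.
- **Sex:** the gain is probably small, 0 to 3 participants per arm for an assumed 0 to 5 % of residual variance. The reason to include it is agreement with the stratified randomisation.
- **Weight loss:** this is the more serious fault in the same sentence. Its size cannot be computed from the article.

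This is worth correcting because the remedy is nearly free and two-sided power at 62 per arm, on the change-variance reading, is only 70.2 % without adjustment.

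**What to change.** Pre-specify the primary model in one of two forms:

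- week-12 MetS-Z with fixed effects for arm, baseline MetS-Z and sex; or
- a linear mixed model on both visits with the baseline mean common to all arms, plus sex and sex-by-time. This form stays closest to the present wording and keeps participants who have only a baseline value.

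Keep age only if it is fixed in advance, and drop the conditional wording. State that weight loss is not in the primary model; any analysis adjusted for it should be labelled exploratory. The cost is a change of wording, best made before unblinding, and a few model degrees of freedom. It needs no new data and no change to recruitment.

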The MetS-associated CVD risk is modifiable with lifestyle behaviours such as dietary modification, which are the first-line treatment, followed by medications when required^(5,9)^. A Mediterranean style of eating, characterised by high consumption of olive oil, fruits, vegetables, whole grains and fish^(10)^, has emerged as a highly recommended dietary pattern for MetS and CVD, endorsed by many organisations including the American Heart Association^(11)^, National Heart Foundation of Australia^(12)^, WHO^(13)^ and healthcare professionals for cardiovascular health^(14,15)^.

Another emerging dietary approach to manage cardiometabolic risk and insulin resistance, obesity and type 2 diabetes (T2D) is the use of lower carbohydrate (LC) diets. The consumption of dietary carbohydrate elevates blood glucose concentrations more than other macronutrients, thereby increasing insulin secretion and placing greater demand on the pancreas^(16,17)^. Consuming a diet that is lower in carbohydrates has been shown to improve insulin sensitivity, glucose metabolism, dyslipidaemia and inflammation^(18–23)^ – conditions often associated with MetS. In recent years, the American Diabetes Association and Diabetes Australia have produced position statements for the use of low-carbohydrate diets in the prevention and treatment of obesity and T2D^(24–26)^.

Combining the Mediterranean diet with an LC approach, that is, reducing carbohydrate intake whilst retaining whole grain foods and increasing *n*-3 fatty acids from fish, nuts and olive oil, was the focus of two earlier studies in people with T2D^(27,28)^. Elhayany *et al*. reported significantly greater reductions in body weight (−10·1 kg), HbA1c (−2 %), plasma TAG (−1·3 mmol/l) and HDL-cholesterol (0·1 mmol/l) following 12 months of a low-carbohydrate Mediterranean approach compared with a low-fat dietary pattern^(27)^. Similarly, Esposito *et al*.^(28)^ reported improved HbA1c (−1·2 %) and plasma HDL-cholesterol (0·10 mmol/l) in people with T2D, and after 4 years of a low-carbohydrate Mediterranean approach, only 44 % of participants required medication compared with 70 % in the low-fat group^(29)^. However, in the time since publication of these studies, there have been no further randomised controlled trials (RCT) to test the effects of the low-carbohydrate Mediterranean diet on different population groups and none in prevalent health conditions such as MetS.

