The primary aim of this RCT is, therefore, to investigate the effects of a lower carbohydrate Mediterranean (LCM) dietary pattern compared with two other diets, namely, traditional Mediterranean (TM) and an LC diet, on the MetS-Z in adults with MetS. The hypothesis is that the LCM dietary pattern will have the greatest impact on reducing the MetS-Z score compared with the other two diets. Secondary outcomes include the effects of the dietary approaches on individual CVD risk factors, endothelial function, arterial stiffness, erythrocyte fatty acids, body composition and plasma inflammatory markers.

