### Primary outcome

#### Metabolic syndrome severity Z score

The MetS-Z will be calculated using sex, ethnicity, BMI (height and weight), systolic blood pressure and finger-prick values of fasting plasma HDL-cholesterol, TAG and glucose and is assessed pre- and post-intervention for all participants. The MetS-Z score was developed in 2014 and has since been validated by various studies^(39)^. The score will be calculated pre- and post-intervention using the online calculator available at https://metscalc.org/metscalc/.

Participants will attend the University of Wollongong after a 10–12 h fast to have a capillary blood collection taken for measures of fasting plasma glucose and lipids. Fasting glucose will be measured using a HemoCue glucose analyser (HemoCue Glucose 201 RT glucose; HemoCue AB), and fasting plasma lipids will be measured using a Cobas® b 101 system (Roche Diagnostics). Waist circumference will be measured in duplicate by a researcher using standardised guidelines halfway between the last rib and the iliac crest^(40)^ with an anthropometric tape. Weight will be measured using calibrated body mass scales, without footwear and light clothing, and repeated in the same manner pre- and post- intervention. Resting blood pressure will be measured using an automated blood pressure monitor in the supine position. 24-h blood pressure will also be measured using an Oscar2 ambulatory blood pressure monitor (SphygmoCor interfacing, SunTech Medical), which is worn over a 24-h period and inflates every hour to measure blood pressure and pulse wave analysis.

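### The protocol allows weight loss, a post-randomisation variable that also feeds MetS-Z through BMI, as a covariate in its only intention-to-treat model; used there, it would change the question the primary analysis answers.

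*Protocol article*

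**What the plan says.** The Statistical analysis section of the protocol article describes one intention-to-treat model, a linear mixed model. In the same sentence it adds that "covariates (age, weight loss) will be added to the model if required in consultation with a biostatistician". It does not confine the weight-loss term to a secondary, sensitivity or mediation analysis.

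The section on the primary outcome defines the score: "The MetS-Z will be calculated using sex, ethnicity, BMI (height and weight), systolic blood pressure", together with fasting HDL-cholesterol, TAG and glucose. Body weight is measured at both ends of the 12 weeks ("repeated in the same manner pre- and post- intervention"), so weight loss is a change that happens after randomisation.

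The aim, at the end of the introduction, is the effect of the lower carbohydrate Mediterranean diet (LCM) "compared with two other diets, namely, traditional Mediterranean (TM) and an LC diet, on the MetS-Z in adults with MetS". The Discussion says the trial will establish which of the three diets reduces MetS severity most. Neither place limits the question to an effect independent of weight.

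**The concern.** Adjusting a randomised comparison for a variable that the treatment can change alters what is estimated. Three features make weight loss unsuitable here.

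- **It follows allocation.** The introduction itself treats weight as something diet can move. It cites a trial in type 2 diabetes in which a low-carbohydrate Mediterranean diet "reported significantly greater reductions in body weight" than a low-fat pattern.
- **It is part of the outcome.** Weight enters MetS-Z through BMI, so the adjusted model holds one component of the outcome fixed while comparing the diets on the whole.
- **Randomisation does not protect the adjusted contrast.** Adherence, for example, can drive both weight loss and the other metabolic changes. Conditioning on weight loss can then introduce bias in either direction.

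At stake is the meaning of the primary result. The trial asks which diet lowers MetS-Z most, by whatever route. The weight-adjusted model asks which diet lowers it most among people with equal weight change, and it could give a different size of effect.

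**Working it through.** **1. Inputs from the Statistical analysis section.** The plan states a "5 % significance level with a variance and change of 0·2 in the MetS-Z score", 80% power and 62 per group. I read this as a difference of 0.20 and a variance of 0.2, so SD = √0.2 = 0.447. Sidedness is not stated.

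**2. The plan's own figure.** n per group = 2 × (z₁₋α + z₀.₈)² × variance / difference².
- One-sided 5%: 2 × (1.645 + 0.842)² × 0.2 / 0.04 = 61.8, so 62 per group and 186 in total. This reproduces the plan.
- Two-sided 5%: 2 × (1.960 + 0.842)² × 0.2 / 0.04 = 78.5, so 79 per group.

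The sample size is not disputed here. The check shows why two-sided power at 62 per arm starts at about 70% rather than 80%.

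**3. What the adjusted model estimates.** Total effect = part not through weight + part through weight. With weight loss in the model, the diet coefficient estimates only the first part, and it does so without bias only if weight loss and MetS-Z share no unmeasured cause. If a share *s* of a 0.20 difference runs through weight, the adjusted target is 0.20 × (1 − *s*). The documents give no value for *s*, so 25%, 50% and 75% are assumptions.

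**4. Power at the adjusted target.** The standard error of a two-arm difference is √(2 × 0.2 / 62) = 0.0803. Dividing the target by 0.0803 gives the noncentrality. The two-sided column uses the noncentral t with 122 degrees of freedom; the one-sided column uses the normal approximation that reproduces 62. Residual SD is held at 0.447.

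| Share through weight (assumed) | Target | Noncentrality | Power, two-sided 5% | Power, one-sided 5% |
|---|---|---|---|---|
| 0% | 0.20 | 2.49 | 70% | 80% |
| 25% | 0.15 | 1.87 | 46% | 59% |
| 50% | 0.10 | 1.25 | 23% | 35% |
| 75% | 0.05 | 0.62 | 9% | 15% |

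**5. Check on the fixed residual SD.** The covariate also removes some residual variance. A simulation allowed for this, with 62 per arm, an assumed 2 kg between-arm difference in weight change with SD 3.5 kg, a two-sided test and no shared cause. At shares of 0%, 25%, 50% and 75%, the unadjusted estimate stayed at about −0.20 with power of 68–70%. The adjusted estimate was −0.20, −0.15, −0.10 and −0.05, with power of 66%, 45%, 26% and 12%. The table is slightly pessimistic at the larger shares, but the pattern is the same.

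**6. Direction.** Let *r* be the within-arm correlation of weight change with MetS-Z, and let 3.5 kg be the SD of weight change (both assumed). The adjusted estimate is then about −0.20 + *r* × (0.447 / 3.5) × (extra kg lost on the better diet). At *r* = 0.5 the slope is 0.064 per kg:
- better diet loses 1 kg less: −0.26
- no difference: −0.20
- 0.5 kg more: −0.17
- 1 kg more: −0.14
- 2 kg more: −0.07

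**The case against.** The strongest reply is that the adjustment is conditional and made with a biostatistician, that an unadjusted model is the natural default, and that an unseen analysis plan may settle when and where covariates enter. That has force as far as the missing trigger goes, and I do not count the missing trigger alone as a fault. It does not answer the main point. The article names an unsuitable covariate for the only intention-to-treat model it describes, and whoever writes or follows the analysis plan could use it there.

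The second reply is that the arms may not differ in weight loss. All three use the same equation for energy requirements, no energy deficit is stated for any arm, and the two lower carbohydrate arms share macronutrient targets. The weight result cited in the introduction was against a low-fat diet, in type 2 diabetes, over 12 months. This stands. The documents do not establish a between-arm weight difference, and without one the adjustment shifts the estimate little. But no weight-maintenance aim is stated either and food is not provided, so any difference that does arise is a consequence of allocation and belongs in the total effect.

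A reader might infer more than the documents support:
- **That the diet effect will be partly removed.** The covariate is optional, and the shift depends on the size and direction of any weight difference.
- **That the ranking of diets could reverse.** With the formula in the working, the sign changes only in an extreme case: an extra 3 kg lost with *r* = 0.7 gives +0.07.
- **That the covariate would discard dropouts from the intention-to-treat set.** Someone without a week-12 weight has no BMI and so no week-12 MetS-Z. What would be lost is mainly baseline-only records, which say little about the 12-week contrast.

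**Conclusion.** The point holds as a fault in a stated choice. Adding weight loss to the intention-to-treat model would replace the total diet effect with a contrast that does not match the aim and that randomisation does not protect. This follows from when weight is measured and how MetS-Z is built, and needs no numerical assumption.

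The size does rest on assumptions. If the arms differ in weight loss, the adjusted effect moves towards zero when the better diet loses more, away from zero when it loses less, and hardly at all when there is no difference. For mediated shares of 25% to 75% of a 0.20 difference, the target falls to between 0.15 and 0.05, and two-sided power falls from about 70% to between 46% and 9%. These figures take a variance of 0.2, 62 per arm and an unchanged residual SD. They illustrate what could happen and do not forecast it.

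**What to change.** In the Statistical analysis section, remove weight loss from the covariates for the primary intention-to-treat model. Adjust only for baseline variables fixed in advance: age, sex as the stratification factor, and baseline MetS-Z, entered either as a covariate or as the baseline measurement in the mixed model. If the role of weight is of interest, report a weight-loss-adjusted or mediation analysis separately, as exploratory, labelled as not the intention-to-treat effect and with its assumption about shared causes stated.

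The cost is one sentence in the protocol and the same in the analysis plan. Sample size, visits and data collection do not change.
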